### Statistical analysis

2.9

Continuous data will be analysed with the independent T-Test (or Mann-Whitney U test for non-normal distribution of data). Categorical data will be analysed using the chi-squared test (two groups) or ANOVA (> two groups). The One-way ANOVA test (or Kruskal Wallis test for non-normal distribution of data) will be used to analyse >two continuous data categories. The impact of multiple variables on allocation is analyzed using the multinomial regression analysis. All statistical tests are considered significant at P < 0.05. Statistical analysis will be performed on the latest version of IBM SPSS Statistics or R.

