**Methods:**

The REHAB + study is a multicenter, prospective, matched controlled, observational study that includes (N)STEMI patients eligible for cardiac rehabilitation. We aim to enroll 300 participants for cardiac telerehabilitation and 600 for center-based cardiac rehabilitation. Participants opting for cardiac telerehabilitation (REHAB+) will be matched with center-based cardiac rehabilitation participants. Additionally, characteristics of patients unwilling to participate in either center-based rehabilitation or telerehabilitation but are willing to share their demographics will be collected. The primary endpoint is quality of life measured with the SF-36 questionnaire at three and twelve months, with patient-related characteristics driving intervention choice as the most important secondary endpoint. Secondary endpoints include physical activity, modifiable risk factors, and digital health experience. The trial is registered at clinicaltrials.gov with registration number NCT05207072.

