Previous research (7) explored the factors leading to non-participation in a telerehabilitation trial. Results show that factors leading to non-participation in this telerehabilitation trial (7) are associated with a worse cardiovascular risk profile (e.g., high age, a higher prevalence of modifiable risk factors, lower exercise capacity), lower prevalence of high education, lower prevalence of employment, and shorter travelling distance to the nearest hospital. Our hypothesis matches these results i.e., that patients not interested in CTR have a worse cardiovascular risk profile, a lower social economic status, and live closer to the nearest hospital than patients who are interested. The REHAB + study is the first large (>150 patients) multicenter and multinational prospective observational study to evaluate the effect of cardiac telerehabilitation in daily practice. It provides the possibility to gain experience with implementing cardiac telerehabilitation. Our study design differs from previous research by its size, design (observational instead of RCT) and inclusion in different European centers and countries. It provides beneficial information about patient characteristics and results. The aim of the REHAB + trial is to identify which parameters influence the decision to participate in center-based CR, CTR, or decline participation in CR. We will compare quality of life, physical activity, and modifiable risk factors before, during and after program completion. We expect an improvement in quality of life, specifically the physical component, in both center-based CR and CTR.

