### Treatment allocation

2.3

The coaches and investigators are explicitly instructed to refrain from advising patients on their choice between CTR and center based CR to avoid bias. However, coaches and investigators are allowed to advise patients to participate one of either CR programs, as that is common practice. Providing neutral information about the advantages and disadvantages of both treatment options is allowed. After signing, all participants are free to choose between CTR and center-based CR. Non-participants are registered as such, provided they meet eligibility criteria and sign informed consent. The patients meet with the nurse after an exercise test to inform them of their allocation choice. The flowchart of the inclusion procedure is found in Figure 1.

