### Limitations

3.1

Although the implementation of CTR might be as (cost-) effective as center-based CR, there could be a learning curve at the start of this newly implemented CR program. Center-based CR and CTR could vary in frequency, intensity, duration and initiation of the program. However, this could be a strength when patients are allowed to compare the programs and choose which one fits them best. It could lead to improved participation in CR.

The coaches of the REHAB + application will use the remote communication feature to frame motivational texts or video’s to benefit long-term uptake of the exercise program. The ability to track behavioral health goals in CTR is a feature that lacks in center-based CR. The frequency of in-person exercise training sessions might initially favor center-based CR short-term on quality of life and exercise goals. However, the ability to track health behavioral goals and the ability to use the application for over nine months might favor CTR long-term.

Local differences may occur due to the unique features that each CR center might implement additionally to local or international guidelines. A learning curve for CR centers without experience with CTR is expected to occur. The nature of treatment allocation of REHAB + results in selection bias, which does resemble daily clinical practice. There is also the possibility that the expected ratio of 1:2 center-based CR and CTR will not be met, as participants have the freedom to choose their CR modality.

Due to the nature of the study, in which clinical practice is closely evaluated, the use of a follow-up exercise test to evaluate physical activity after CR was not feasible. Therefore, the choice for a less rigorous method of physical activity evaluation was chosen, namely by questionnaire which could have recall bias. Participants will have a baseline exercise test to evaluate their physical condition.

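### Section 2.9 states no outcome analysis that adjusts for confounders or accounts for the matched sets in self-selected groups, and its test is not the one named in section 2.8

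*Protocol article*

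**What the plan says.** Allocation is by patient preference (section 2.3): "After signing, all participants are free to choose between CTR and center-based CR". The Abstract calls the study a "multicenter, prospective, matched controlled, observational study" and adds: "Participants opting for cardiac telerehabilitation (REHAB+) will be matched with center-based cardiac rehabilitation participants". Section 2.8 plans for about 600 center-based patients so that 300 telerehabilitation (CTR) patients can be matched. The article names no matching variables and no matching method.

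On the endpoint, the Abstract says: "The primary endpoint is quality of life measured with the SF-36 questionnaire at three and twelve months". Section 4 undertakes to compare the effectiveness of the two programmes.

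Section 2.9 gives the analysis for two groups: "Continuous data will be analysed with the independent T-Test (or Mann-Whitney U test for non-normal distribution of data"). It adds chi-squared tests, ANOVA or Kruskal-Wallis for more than two groups, and a multinomial regression whose outcome is allocation. It does not mention SF-36, baseline score, centre or matched sets. Section 2.8 bases the sample size on the change in the SF-36 physical component score over a year and names a Hotelling-Lawley trace test, which section 2.9 does not take up.

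The Introduction expects that "patients not interested in CTR have a worse cardiovascular risk profile, a lower social economic status, and live closer to the nearest hospital". Section 3.1 concedes: "The nature of treatment allocation of REHAB + results in selection bias, which does resemble daily clinical practice". It also says: "Local differences may occur due to the unique features that each CR center might implement additionally to local or international guidelines".

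**The concern.** The two programme groups form by choice, and the protocol expects choice to be related to cardiovascular risk, social economic status and distance from hospital. These could plausibly bear on later quality of life. Centre may matter too: section 2.6.2 lets each centre structure its own exercise training, and uptake of CTR may differ between centres.

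A two-sample test without covariates attributes to the programme whatever difference remains between the groups. Matching is the only stated protection, and nothing in section 2.9 corrects what it leaves behind. Where matching does succeed, the stated test treats related observations as independent.

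Sections 2.8 and 2.9 also point to different primary analyses. A reader cannot tell whether raw follow-up scores, change scores or a multivariate set of scores will be tested. At stake is whether the primary SF-36 result can be read as more than a description of who chose which programme.

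**Working it through.** **1. The plan's own figure.** Section 2.8 gives 12-month PCS means of 53.3 (reference) and 55 (CTR), so a difference of 1.7. It also gives SD 7.0 for CTR, alpha 0.05 and power 0.80. I assume a two-sided test and SD 7.0 in both groups.

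n per group = 2 × (1.960 + 0.842)² × 7.0² / 1.7² ≈ 266.2, or 267. With the t distribution it is 267.12, rounded up to 268, which is the stated figure. Dropout: 268 / 0.90 = 298, rounded to 300. The stated number is thus what an unadjusted two-sample t-test would need, although section 2.8 names another test.

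**2. Residual baseline imbalance, raw 12-month scores.** Inputs: 270 per group (300 less 10%), SD 7.0 and baseline SD 5.8 (section 2.8). Assumed: a slope of 12-month on baseline PCS of 0.5, and the size of the gap left after matching.

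- SE = √(2 × 49 / 270) = 0.602
- Bias = gap in SD × 5.8 × 0.5
- False-positive rate = P(|Z + bias/SE| > 1.96), with no true programme effect

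| Residual gap | Points | Bias | Share of 1.7 | Bias/SE | False-positive rate |
|---|---|---|---|---|---|
| 0.1 SD | 0.58 | 0.29 | 17% | 0.48 | about 8% |
| 0.3 SD | 1.74 | 0.87 | 51% | 1.44 | about 30% |
| 0.5 SD | 2.90 | 1.45 | 85% | 2.41 | about 67% |

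**3. The same gap, change scores.** Bias = (0.5 − 1) × gap, so −0.29, −0.87 and −1.45 points. Variance of change = 49 + 33.64 − 2 × 0.5 × 33.64 = 49, so the SE is again 0.602. The false-positive rates are unchanged and the sign reverses.

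**4. A check that does not use the slope.** Suppose selection leaves an uncontrolled difference of 0.5, 1.0 or 1.7 points in the outcome, from any source, and there is no programme effect. These sizes are assumptions. SE = 7 × √(1/n₁ + 1/n₂).

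- 268 per group (SE 0.605): significant in 13%, 38% and 80% of studies.
- 300 versus 600 (SE 0.495): 17%, 52% and 93%.

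A larger center-based group narrows the SE but leaves the bias unchanged, so the error rate rises.

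**5. If matching works.** Assume 1:1 pairs with a within-pair outcome correlation r of 0.2 to 0.4. The correct SE is √(1 − r) times the independent-samples SE. The latter is therefore 1/√0.8 = 1.12 to 1/√0.6 = 1.29 times too large (12% to 29%). Actual alpha = 2 × [1 − Φ(1.96/√(1 − r))] = 2.8% to 1.1%. The test is then conservative.

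**6. Sample size under baseline adjustment.** Adjustment for baseline alone needs about 268 × (1 − ρ²) per group: 244, 201 and 137 for an assumed baseline to 12-month correlation of 0.3, 0.5 and 0.7. It does not call for more patients.

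**The case against.** The strongest reply is that matching is a design feature. A t-test on a well matched sample does benefit from it, because matching controls confounding through the choice of controls. The matching variables may well be in the full protocol or the analysis plan, and a condensed article need not list them. This stands. A reader might infer that matching plays no part in the comparison. The documents do not support that. They show only that the stated test has no term for the matched sets and no adjustment for what matching leaves.

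A reader might also infer that the bias favours CTR. That does not follow either. The Introduction contrasts patients who are and are not interested in CTR. The uninterested include people who decline all rehabilitation and contribute only baseline data (section 2.7), so it is not a prediction about CTR versus center-based participants, least of all after matching. The sign of the baseline bias also depends on whether raw or change scores are tested, and the wording of section 2.8 leans towards change.

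Third, the primary p-value need not be misleading in every case. If matching works, the independent test costs power and does not inflate false positives.

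Two replies carry less weight. Section 3.1 discloses selection bias and centre differences, but disclosure does not remove bias from an effectiveness comparison. Change scores would use the baseline value, but they still leave risk profile, social economic status, distance and centre unadjusted, and step 3 shows that they carry a bias of their own. Nor is this a matter of silence that an analysis plan could fill: section 2.9 states a test and reserves its one multivariable model for allocation.

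**Conclusion.** The point holds in this form: for self-selected groups, section 2.9 states an unadjusted independent-samples test, names no outcome analysis that adjusts for baseline SF-36, centre or the expected drivers of choice or accounts for the matched sets, and does not agree with section 2.8.

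The planned difference is only 1.7 points, so modest residual imbalance matters. The rates of about 8%, 30% and 67% are scenarios, not forecasts. They rest on assumed gaps of 0.1, 0.3 and 0.5 SD remaining after matching and on an assumed slope of 0.5, and no figure in the article fixes either. The alternative case, an actual alpha of about 2.8% to 1.1%, assumes 1:1 pairs that are correlated at 0.2 to 0.4, whereas the recruitment targets are 300 and 600. The two cases are alternatives and differ in kind: the first risks a false claim, the second a missed effect. The arithmetic behind 268 per group is sound; the fault lies in the stated analysis.

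**What to change.** In section 2.9, before outcomes are analysed:

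- Analyse the CTR versus center-based SF-36 outcomes at 3 and 12 months by regression on baseline score, centre and prespecified T0 confounders. Candidates already collected are age, sex, employment, distance, risk factors, infarct type, revascularisation, LVEF and the baseline exercise test.
- Use standard errors that account for the matched sets.
- Report covariate balance after matching, and describe the result as an adjusted association.
- State one primary test and bring sections 2.8 and 2.9 into line on it, including whether raw or change scores are meant.
- Keep the unadjusted tests for descriptive baseline comparisons.

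Propensity-score matching within centre or overlap weighting would also be acceptable; the choice is the sponsor's.

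The cost is wording and modest extra analysis, with no new data. One downside is that some CTR patients may lack comparable center-based matches, more so if the expected 1:2 ratio is not met, as section 3.1 warns. Unmeasured differences will remain whatever model is used.

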The main source of baseline data extraction is the electronic medical file, besides questionnaires. Baseline characteristics include age, sex, ethnicity, employment status, marital status, living situation and distance from the hospital. Traditional risk factors data collection include a medical history of hypertension, hypercholesterolemia and diabetes (including HbA1c), current smoking status and family history of cardiovascular disease. Moreover, a researcher from the research team extracts the medical reason for CR participation, medical history relevant to cardiovascular diseases and the current use of cardiovascular medication. Finally, information from focus tests, such as heart ultrasound (LV function), coronary angiography (with or without modes of revascularization) and electrocardiography will be interpreted and obtained by a medical doctor from the research team. Finally, results from the exercise test include blood pressure, peak blood pressure, METS score and ECG changes at peak exercise capacity.

The REHAB + app monitors adherence and compliance of CTR participants. Adherence is defined as the number of dropouts and the reason for drop-out in relation to participants completing CTR. Compliance is defined as the number of logins and the proportion of planned exercise sessions completed, as well as which sessions are completed (i.e., exercise, quitting smoking). Information from i.e., the heart rate monitor, goal progression, data input by the participant (e.g., BORG scale) and interaction with the coaches will be logged in the app.

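### Section 2.9 names ANOVA for categorical data in more than two groups; for nominal characteristics with three or more levels, the three-group p-values would depend on arbitrary category codes

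*Protocol article*

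**What the plan says.** Section 2.9 of the protocol article gives this rule for categorical variables: "Categorical data will be analysed using the chi-squared test (two groups) or ANOVA (> two groups"). The next sentence deals with continuous variables separately: "The One-way ANOVA test (or Kruskal Wallis test for non-normal distribution of data) will be used to analyse >two continuous data categories". The section then adds a multivariable analysis, "The impact of multiple variables on allocation is analyzed using the multinomial regression analysis", and one threshold for everything: "All statistical tests are considered significant at P < 0.05".

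The Introduction gives the study's aim as to "identify which parameters influence the decision to participate in center-based CR, CTR, or decline participation in CR", which makes three groups. The Abstract ranks "patient-related characteristics driving intervention choice as the most important secondary endpoint". On the variables, section 2.7 says: "Baseline characteristics include age, sex, ethnicity, employment status, marital status, living situation and distance from the hospital". Table 2 marks baseline characteristics as collected in all three groups, and its footnote b adds, among others, mode of revascularization and type of acute coronary syndrome.

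**The concern.** ANOVA tests whether group means are equal, and a nominal variable has no mean. Following the rule on marital status, for example, means giving each category a number and comparing average code numbers across the three groups. With three or more categories, a different numbering of the same patients gives different averages and a different p-value. The chi-squared test ignores the labels and accepts a table of any size, so there is no statistical reason to confine it to two groups.

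At stake are the one-variable-at-a-time comparisons of center-based CR, CTR and non-participants, which bear on the highest-ranked secondary endpoint. A real difference in a multi-level characteristic could be missed, or an apparent one produced, by the order in which categories happen to be coded.

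**Working it through.** **Does a lenient reading remove the problem?** One could suppose that ANOVA was meant only for continuous variables. The two sentences side by side rule this out. The first has categorical data as its subject and sends them to ANOVA beyond two groups. The second sends continuous data to one-way ANOVA or Kruskal-Wallis. Nothing elsewhere in the article extends chi-squared to three groups.

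**The plan's own figure.** The only computed figure is 268 per group. With the stated 12-month scores, the difference is 55 − 53.3 = 1.7. Taking SD 7.0, two-sided alpha 0.05 and power 0.8, n = 2 × (1.960 + 0.842)² × (7.0/1.7)² ≈ 267 per group; the t-based version gives 267.12, rounded up to 268. No categorical test enters it, so this point does not touch it.

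**Inputs for the illustration.** Planned sizes are 300 for CTR and 600 for center-based CR (Abstract). The number of non-participants is not given; 200 is assumed. All cell counts are invented.

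| Group | A | B | C | D | Total |
|---|---|---|---|---|---|
| CTR | 60 | 180 | 40 | 20 | 300 |
| Center-based CR | 120 | 360 | 30 | 90 | 600 |
| Non-participants | 40 | 100 | 40 | 20 | 200 |

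**Chi-squared.** X² = Σ(O − E)²/E with E = row total × column total / 1,100. The result is X² = 53.6 on (3 − 1)(4 − 1) = 6 df, p = 9e-10, whatever the labels.

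**ANOVA on codes.** F = between-group mean square / within-group mean square of the code numbers, on 2 and 1,097 df, repeated over all 4! = 24 ways of assigning 1 to 4 to A to D. Three of them:

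| Codes for A, B, C, D | Mean code: CTR / center-based / non-participants | F | p |
|---|---|---|---|
| 2, 3, 1, 4 | 2.60 / 2.85 / 2.50 | 19.5 | 5e-9 |
| 1, 2, 3, 4 | 2.07 / 2.15 / 2.20 | 1.58 | 0.21 |
| 1, 4, 3, 2 | 3.13 / 3.05 / 3.00 | 0.79 | 0.45 |

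As an arithmetic check, the CTR mean under 1, 2, 3, 4 is (60×1 + 180×2 + 40×3 + 20×4)/300 = 620/300 = 2.07. Of the 24 codings, 18 give p < 0.05 and 6 do not.

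**Both directions of error.** Two further invented tables, with 150 non-participants assumed:
- Three levels, rows 60/180/60, 180/240/180 and 45/60/45: chi-squared p = 6e-7. Under codes 1, 2, 3 every group mean is exactly 2, so ANOVA gives p = 1.0.
- Four levels, rows 180/60/30/30, 360/90/75/75 and 90/15/22/23: chi-squared p = 0.081. ANOVA runs from 0.009 to 0.998, and 4 of 24 codings fall below 0.05.

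**Two-level variables.** Rows 225/75, 420/180 and 98/52: ANOVA p = 0.0860 under either coding, chi-squared p = 0.0859. With two levels, recoding only reverses or rescales the scale, which leaves F unchanged.

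**The case against.** The strongest reply concerns reach. Four parts of it stand.

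- The question of what drives the choice has its own method in section 2.9, the multinomial regression. That model does not depend on the ANOVA sentence, provided nominal predictors enter as factors. A reader might infer that the top secondary endpoint is invalidated. The document does not support that; only the univariable three-group comparisons beside the regression are affected.
- A reader might also infer that every categorical characteristic is at risk. Code dependence needs at least three levels. Sex, STEMI versus NSTEMI (the only infarct types admitted by Table 1) and yes/no histories such as hypertension or diabetes have two. The article gives no number of levels for the remaining variables, so how many are affected is not established.
- Follow-up results are out of reach. Non-participants contribute baseline data only (section 2.7), so later comparisons, including SF-36, involve two groups, and SF-36 is a score rather than a category.
- The counts are invented, and in the main example 18 of 24 codings lead to the same conclusion as chi-squared.

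It may also be said that the sentence is a slip and that any analyst would use chi-squared. That is possible, but then the analysis would depart from its published plan. Nor is this a detail left to a fuller document: the article states a specific rule, and the rule is wrong.

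**Conclusion.** The rule is wrong as written and should be fixed. It affects the univariable comparison of center-based CR, CTR and non-participants on nominal baseline characteristics with three or more levels. Ethnicity, employment status, marital status, living situation and mode of revascularization are plausible cases, on the assumption that each is recorded in more than two categories.

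The calculations prove that the p-value can move across 0.05 in either direction through recoding alone. They do not measure how far it would move in this trial, because the cell counts and the number of non-participants are assumed. The primary endpoint, the sample size, the two-group comparisons and a properly specified multinomial regression are not in doubt, which is why this is a should-fix point rather than a threat to the study's main result.

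**What to change.** Replace the sentence on categorical data in section 2.9 with: *Categorical data are compared with the chi-squared test for any number of groups, or with the Fisher-Freeman-Halton exact test when expected counts are small.* Keep one-way ANOVA and Kruskal-Wallis for continuous or ordinal data in more than two groups. Fagerström class should not be cited as an ordinal example there, since Table 2 collects that test only in the two CR groups. It would also help to state that nominal predictors enter the multinomial regression as factors.

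The cost is one or two sentences. Standard software covers these tests, and no data item, design feature or sample size changes.

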### Study population

2.2

Patients eligible for CR who are unwilling to participate in either CTR or center-based CR are allocated to the non-participation category of the study. Patients eligible for the trial are (N)STEMI patients over 18 years old that meet the eligibility criteria to participate in a CR program. Eligibility criteria for CR include the physical ability to safely perform an exercise test. Patients with myocardial ischemia during the exercise test, and judged unsafe for CR participation by a trained cardiologist, are excluded from the trial. Patients are required to have the mental ability to cooperate by following instructions from their coaches and need the proper knowledge to comprehend the native language of the coaches. Patients participating in CR at a different CR center during or after hospitalization are excluded. The research nurse and cardiologist reserve the right to exclude patients deemed unfit for CR due to severe comorbidities. A complete overview of in- and exclusion criteria is found in Table 1.

**Table 1 T1:** In- and exclusion criteria for cardiac (tele) rehabilitation.

Inclusion criteria	
CR	Recent myocardial infarction [(N)STEMI only]
CR	Signed written informed consent
CTR only	Smartphone capable of installing REHAB + application
Exclusion criteria	
CR	Contra-indication for CR (such as risk for safety and limited lifespan)
CR	Mental impairment leading to an inability to cooperate
CR	Severe impaired ability to exercise (including an inability to safely perform the exercise test)
CR	Insufficient knowledge of the native language
CR	Current participation in CR (at CR center or elsewhere)
CR	Participation in a CR program elsewhere after index myocardial infarction

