### Data collection

2.7

Data are collected at program initiation (T0), three months after initiation (T1) and twelve months after initiation (T2). Data collection from non-participants only include baseline characteristics at T0. Researchers collect data from the electronic health record. Exercise-related data will be collected by Liva (Livahealthcare.com). Data will be made available after all participants completed their CTR program. Participants receive questionnaires by e-email or by postal mail. Participant data is pseudo anonymized. The SPIRIT diagram is found in Table 2.

**Table 2 T2:** SPIRIT diagram for REHAB+ study.

	Study period			
	Enrolment	Allocation	Post-allocation	Close-out
Timepoint^a^	*-t_1_*	0	*t_1_*	*t_2_*
Enrolment:				
Eligibility screen	(X)			
Informed consent	(X)	(X)		
Allocation		(X)		
Interventions:				
Center-based cardiac rehabilitation				
Cardiac telerehabilitation				
Non-participation				
Assessments:				
Baseline characteristics^b^		(X)		
Medication, blood pressure, BMI		(X)	X	X
Blood sampling^c^		X	X	X
Exercise test		X		X
Adherence and compliance			X	X
Adverse (cardiac) events			X	X
Fägerstrom test		X	X	X
SF-36 questionnaire		X	X	X
IPAQ-SF		X	X	X
eHIQ^d^			X	

Cells marked with (X) are data gathered for center-based CR, CTR and non-participants of CR. Cells marked with X are data gathered for both center-based CR and CTR. SF-36 36-Item Short Form Health Survey, IPAQ-SF International Physical Activity Questionnaire-Short Form, eHIQ e-Health Impact Questionnaire.

^a^
-t1= Period between hospitalization and start cardiac rehabilitation, t0 = start cardiac rehabilitation, t1 = three months, t2 = twelve months.

^b^
Demographics, medical history, risk factors, coronary angiography outcome, mode of revascularization, type of acute coronary syndrome, left ventricular ejection fraction and twelve lead electrocardiogram.

^c^
Lipid profile, kidney function and Hb1Ac.

^d^
Participants in the cardiac telerehabilitation group receive an extended questionnaire containing specific questions about the REHAB + app.

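### The choice model cannot separate lack of smartphone access from preference, because a capable phone is a condition for telerehabilitation only and phone access is not among the listed baseline data

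*Protocol article*

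**What the plan says.** The Introduction gives the aim as to "identify which parameters influence the decision to participate in center-based CR, CTR, or decline participation in CR". The Abstract ranks this high: the primary endpoint is SF-36 quality of life, "with patient-related characteristics driving intervention choice as the most important secondary endpoint". Section 2.9 gives the analysis in one sentence: "The impact of multiple variables on allocation is analyzed using the multinomial regression analysis". It does not restrict the model to patients who had every option open to them.

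On who had which option, two places differ. Section 2.3 states: "After signing, all participants are free to choose between CTR and center-based CR". Table 1 in section 2.2 lists one criterion for CTR only: "Smartphone capable of installing REHAB + application".

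Section 2.7 lists the baseline characteristics: age, sex, ethnicity, employment, marital status, living situation and distance from the hospital, followed by clinical variables. Smartphone access is not among them. The Introduction itself notes that older adults use mobile technology less. It hypothesises that patients not interested in CTR have a worse cardiovascular risk profile and lower socioeconomic status.

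**The concern.** A model of choice can be read as preference only if everyone in it had the same options. A patient without a suitable phone does not have the CTR option, whatever that patient would have wanted. The model nevertheless counts the patient as having chosen center-based rehabilitation or as having declined.

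If phone access differs by age or socioeconomic status, part of that difference is transferred to the coefficients for those variables. The article supports the link with age. A link with socioeconomic status is my assumption, though a plausible one. For both variables the distortion runs in the direction of the study's hypothesis, so a result produced partly by access could be taken as confirmation. With no access variable in the data, the analyst could not tell the two apart.

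**Working it through.** **The plan's own figures.** The article gives no figure for the choice model, so there is none to reproduce. Its sample size concerns the SF-36 physical component. It reproduces (difference 55 − 53.3 = 1.7, SD 7.0: 267 per group by the normal formula, 268 by the t-test), but this point does not depend on it.

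**Inputs from the article.** The expected CTR to center-based ratio is 1:2 (section 2.8), so the share choosing CTR is p = 1/3. The target is 300 + 600 = 900 participants.

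**Assumed inputs.** Ownership of a capable phone is s₁ in younger and s₂ in older patients. Preference for CTR is 1/3 at every age, so the true odds ratio is 1.00. Patients without a phone who would have wanted CTR enter center-based rehabilitation. For the significance column, 40% of the 900 are older (540 younger, 360 older).

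**Formulas.** The observed CTR share is s·p, so

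apparent OR (older vs younger) = [s₂p / (1 − s₂p)] / [s₁p / (1 − s₁p)].

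The chance that this false effect reaches P < 0.05 is Φ[(|s₁p − s₂p| − 1.96·SE₀) / SE₁], with SE₀ the pooled and SE₁ the unpooled standard error of the difference in proportions.

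| Assumed ownership, younger/older | Observed CTR share | Apparent OR | Chance of P < 0.05 |
|---|---|---|---|
| 100% / 95% | 0.333 / 0.317 | 0.93 | about 7% |
| 98% / 90% | 0.327 / 0.300 | 0.88 | about 13% |
| 95% / 80% | 0.317 / 0.267 | 0.78 | about 36% |
| 95% / 70% | 0.317 / 0.233 | 0.66 | about 78% |
| 95% / 60% | 0.317 / 0.200 | 0.54 | about 98% |

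Worked line for 95%/70%: 0.317/0.683 = 0.463 and 0.233/0.767 = 0.304, so OR = 0.304/0.463 = 0.66.

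**Significance is not assured.** With 450 patients in each age group instead, 95%/70% gives SE(log OR) = 0.151 and z = −2.79 (p about 0.005). At 98%/85% the OR is 0.81, with z about −1.41 and p about 0.16.

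**If patients without a phone decline instead.** The odds of CTR against center-based are then s·(1/3)/(2/3) = s/2, and the apparent OR is s₂/s₁. Over the same rows this runs from 0.95/1.00 = 0.95 to 0.60/0.95 = 0.63. The distortion is smaller but has the same sign.

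**Check in a multinomial model.** In 200,000 simulated patients (25% declining, the rest 1:2, ownership 95%/70%, preference unrelated to age), the older-versus-younger OR for CTR against center-based was 0.65 in all patients and 1.00 among phone owners.

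**The case against.** The strongest reply is that uptake is a legitimate target. The study sets out to mirror routine practice and section 2.9 models allocation. In routine practice, not owning a phone is one of the ways in which age affects use of CTR, and restricting to owners would remove that. Section 3.1 also concedes selection bias from free choice. This stands, and it is why the all-patient model should remain. It does not remove the point, because the Introduction speaks of a decision and the Conclusion of patient preference, and for those the two mechanisms must be told apart.

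A second reply is that ownership may be near universal, in which case the effect is small (first row of the table). That is possible, but the listed data cannot show it. An article's variable list may also be incomplete. If the full case report form holds the criterion, the fix becomes easy.

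Four stronger readings are tempting, and the documents do not support them.

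- **The model necessarily reads ineligibility as preference.** The size depends on ownership rates that the article does not give. It can do so; how far is unknown.
- **Non-participants escape the exercise-test screen.** Section 2.2 says "Eligibility criteria for CR include the physical ability to safely perform an exercise test", and Table 2 marks the test with a plain X, where "Cells marked with X are data gathered for both center-based CR and CTR". But section 2.3 says "Non-participants are registered as such, provided they meet eligibility criteria and sign informed consent" and has patients give their choice after an exercise test, and Table 2 marks the eligibility screen for all three groups. Table 2 shows which data are gathered, not who was screened. Section 2.4 ties the test to starting rehabilitation, so there is an ambiguity to resolve, but no demonstrated difference in screening.
- **Missing SF-36, blood or exercise data would delete the non-participants from the model.** Section 2.9 names no covariates, so nothing shows that these variables enter the three-way model.
- **Center-based patients without a phone are invalid matches.** The article does not state the matching variables. Lack of a phone would matter only if it related to outcome after matching, and this is not shown.

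**Conclusion.** The point holds in limited form. As described, the analysis of the most important secondary endpoint cannot distinguish lack of access to CTR from preference against it, and this bears on age and socioeconomic status in particular. For age, a true odds ratio of 1.00 could appear as 0.93 to 0.54 over the ownership range considered. Every ownership rate and age split is an assumption, as is preference being unrelated to age. Near-universal ownership would make the effect negligible. Estimates from the all-patient model remain valid as a description of uptake. This is a worthwhile, inexpensive improvement and does not invalidate the model.

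**What to change.** 1. Code the Table 1 smartphone criterion for all enrolled patients, including non-participants, wherever it can be retrieved.
2. Keep the all-patient multinomial model and label it an analysis of uptake.
3. Add the CTR versus center-based contrast among patients with a capable phone as the analysis of preference, and report those without one as a separate group, *CTR not available*.
4. If the flag cannot be retrieved, limit the conclusion to uptake and do not describe it as preference.
5. Reconcile sections 2.2, 2.3 and 2.4 with Table 2 on whether non-participants undergo the exercise test, and state how the test-based criteria are verified in them.

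The cost is some wording, one added model and a retrospective look-up. Enrolment ended in February 2024, so some flags will be missing, and the added model will have a smaller sample.
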